#### Secondary outcome measures

Number of different preventive services (among the 7 of the study) registered for each individual during the 2006 and 2007 year periods.

#### Other measures

We assess the following factors related to the outcome measures according to the levels of analysis:

Computerized PHCT: variables of structure and organization of the PHCT (number of GPs and nurses, presence of specialists), adherence to PAPPS, training centre for family doctors, ECR system and starting year, assigned population.

Health-care professionals (GPs, nurses): gender, age, specialty, years of employment in PC and in the PHCT, workload (mean number of visits/day), years of experience with ECR.

Subjects: gender, age, comorbidity according to the Adjusted Clinical Groups grouper [40,41], frequency of consultations (visits/year).

#### Information source

The individual data will be extracted directly from the central computer servers of the ECRs of the subjects included in the study. In Navarra and Aragón the system used is OMI-AP and in Catalonia the eCAP system. The data related to health-care professionals and to PHCT will be obtained from an on-line database for health-care professionals and from a person responsible in each centre.

#### Data extraction and processing

Using the specific interface for each specific computer system (OMI-AP and eCAP), each region will extract the study data and transfer them to a central database where they will be homogenized and processed into a specially-constructed final database.

#### Confidentiality of data

Data confidentiality will be assured during and subsequent to the extraction using encryption and dissociation of the individual's identification, health-care professionals, and of PHCTs.

#### Ethical aspects

The study has been favourably evaluated by the Research Committee of the IDIAP Jordi Gol.

#### Quality control

Quality controls will be carried out in the 2 extractions of data comparing agreement between the central database and the original data of some centres as for: number of patient, visits and diagnoses as well as data of prevalence of certain diseases. It will also be checked if the population data is appropriate by comparing it with data from the census and other official sources. In the case of items related to clinical activities (for example blood pressure measurement), any register with missing values will be considered as not performed.

### Statistical analyses

For the first two objectives all the analyses will be performed on a global level and each region separately. Cluster level analysis (computerized PHCT and health-care professional) will be performed using standard parametric or non-parametric analytical methods, with cluster means or proportions as observations [37,42]. For the adjusted analysis we will perform regression analysis of individual level data using methods for clustered data, multilevel, hierarchical or random effects models [37,43]. This methodology facilitates simultaneous analyses of the effects of individual and cluster variables in order to evaluate whether the relationship between variables at the individual level varies in accordance with the characteristics of the cluster and whether the individual and cluster variability can be attributed to factors of the cluster and/or to the factors related to the individual. Analysis will be performed at 3 levels: PHCT, health-care professional and individual subjects.

Multilevel linear (for continuous outcome variables) or logistic (for dichotomous outcome variables) regression analyses will be performed for the first two objectives. The analyses will be adjusted for explanatory factors at individual, health-care professional and PHCT level and for other variables that are clinically relevant. We will also adjust for possible confounders checking whether they will affect the outcomes. A nested or hierarchical structure will be considered: the attended individuals are nested within the health-care professional and the health-care professional within PHCT. The PHCT and the health-care professional will be considered random effects.

Multilevel Poisson regression models will be used to evaluate the number of preventive activities recorded for each individual.

For the third objective, the ICCs, their standard errors and the components of variance [36,37,42,43] for the different outcome measures will be calculated using methods that enable adjustment for covariables, together with random effect methods (health-care professionals and PHCT). Initially, we will estimate the coefficients of variance and ICCs using the outcome as the dependent variable and the health-care professional/PHCT as random effects. Subsequently, we will perform an adjusted analysis for the characteristics of the individual, the health-care professional and the PHCT.

We will study interactions and collinearity. The collinearity of the maximal models will be evaluated using the criteria proposed by Belsley [44]. We will set the significance level at 1% (two-tailed).

Analysis will be carried out using the SPSS statistical package for Windows, version 15 (SPSS Inc., Chicago, IL) and the SAS package 9.1.3 for Windows (SAS Institute Inc., Cary, NC, USA).

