### Setting

The study is set in PHCTs computerized prior to 1st of January 2005 in the regions of Aragón, Navarra, and Catalonia. So far computerization had occurred in 19% of 121 PHCTs in Aragón, 76% of 54 PHCTs in Navarra, and 97.5% of 278 PHCTs in Catalonia (at the Catalan Health Institute).

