### Sample size and randomisation

To achieve the equivalent power of a patient-randomised design, in a cluster randomised design the effective sample size will need to be the standard sample size of a single random sampling multiplied by the design effect [31,37,38]. The design effect is a function of the average cluster (computerized PHCT) size and the (intraclass correlation coefficient (ICC) of the outcome:

design effect = 1 + (n-1)*ICC

where *n *is the average number of individuals sampled per cluster [38].

sWith the cluster design we set an ICC of 0.05 on the assumption that the ICCs estimated for outcome variables from PC are less than 0.05 [28,36,39] and that the average number of individuals sampled per centre is at least of 2,500. Therefore 20 computerized PHCTs are necessary from each region to guarantee a statistical power of 80%, assuming a 50% event rate with an alpha two-tailed significance level of 0.05. Finally, to allow any of the randomised computerized PHCTs declining our offer to participate, we increased the number of computerized PHCTs selected from each region to 22. As such, the total number of subjects included will be more than 300,000 in Aragón, 200,000 in Navarra and 350,000 in Catalunya i.e. more than 850,000 subjects in total. This volume of subjects ensures a good estimate of the different outcome measures in the sub-groups of each cluster.

The selection of computerized PHCT to participate in the study is by a simple random sample within each region. Sample size calculation and computerized PHCT selection is performed with Epidat 3.1.

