## Discussion

The project results will provide very useful information on the degree of registration and performance of the 7 preventive services selected. These 7 activities have been widely implemented and have a high impact on the health of our population [2-6]. The large population database of the study, with more than 850,000 people recorded, will increase considerably the external validity of the results and will reflect usual clinical practice at the Primary Care settings in the Spanish NHS.

This fact may help to overcome the current limitations and to investigate CPV and the factors that have an impact on the implementation of preventive services.

Certainly the source of information used and the ECRs may have limitations. The heterogeneity of current computer systems may complicate the extraction of outcomes and of variables. However, the design of the data extraction interfaces and data transfer will minimize the problems. The lack of exhaustivity in data recording may introduce some distortions in the information. Nevertheless, stability of computer systems at the centres will help to minimize this problem and the quality control measures will help to identify the magnitude of the problem.

Studies based on cluster sampling allow important reduction in costs and greater easiness in administration but require knowledge of the ICCs. For this study ICCs has been estimated from studies conducted in other countries. In our study we will provide information concerning the magnitude of the ICC, evaluate factors that influence their magnitude, estimate within-cluster and between-cluster components of variance for the outcome measures under consideration and determine the sample size; all of these factors will aid the design and statistical analysis of future cluster-based studies set in PC.

In conclusion, the present study will provide new knowledge in:

- The identification of factors related to the variability in the implementation of preventive services, which will facilitate the design of strategies for improvement in the planning and administration of services in PC.

- The assessment of the evolution of the detected health problems will improve the degree of existent evidence taking into account the results of screening and the control of those problems. This will be very useful for the evaluation of the PAPPS and other studies based on this source of information.

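### Pooled descriptive rates give equal weight to teams drawn at about 96%, 54% and 8%, so they do not estimate the three-region computerised frame when regions differ

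*Protocol article*

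**What the plan says.** All in the protocol article:

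- Setting gives the extent of computerisation: "19% of 121 PHCTs in Aragón, 76% of 54 PHCTs in Navarra, and 97.5% of 278 PHCTs in Catalonia". The Catalan figure covers the Catalan Health Institute only.
- Sample size and randomisation derives 20 teams per region, then adds an allowance for refusals: "we increased the number of computerized PHCTs selected from each region to 22". On selection: "The selection of computerized PHCT to participate in the study is by a simple random sample within each region".
- Statistical analyses: "For the first two objectives all the analyses will be performed on a global level and each region separately". The cluster-level analysis is to use standard methods in which each team's mean or proportion is one data point. The individual-level analysis uses multilevel models with team and professional as random effects. Neither description gives region a role as stratum, covariate or weight in the pooled analysis.
- Other measures lists the record system among the team variables, but not region. Information source gives OMI-AP for both Aragón and Navarra and eCAP for Catalonia.
- Discussion says that the large database "will increase considerably the external validity of the results and will reflect usual clinical practice at the Primary Care settings in the Spanish NHS".

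**The concern.** Drawing the same number of teams from three frames of very different size is a disproportionate stratified sample. It serves the regional estimates well. When strata are pooled with every team counting once, however, the result reflects how many teams were drawn per region rather than how many exist.

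At stake are the pooled implementation rates (objective 1), the pooled control rates (objective 2), and the pooled description of spread between teams. The document itself gives reason to expect regional differences. The Background says record systems differ by region in standards and software. Quality control counts a missing clinical-activity entry as not performed, so differences in recording pass straight into the rates.

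**Working it through.** **The plan's own figure.** Design effect = 1 + (2,500 − 1) × 0.05 = 125.95. The document states 80% power, a 50% event rate and two-sided alpha 0.05, but no detectable difference or precision. Either of two assumed targets returns its 20 teams:

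- ±5-point precision: 384.1 × 125.95 / 2,500 = 19.35, so 20.
- 50% against 60%, 388 per group: 388 × 125.95 / 2,500 = 19.55, so 20 per group.

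The requirement is per region.

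**Frames and selection fractions** (Setting; Sample size and randomisation).

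| | Computerised teams | Fraction, 22 drawn | Fraction, 20 taking part | Weight (frame/22) |
|---|---|---|---|---|
| Aragón | 0.19 × 121 = 22.99, about 23 | 95.7% | 87% | 1.05 |
| Navarra | 0.76 × 54 = 41.04, about 41 | 53.7% | 49% | 1.86 |
| Catalonia | 0.975 × 278 = 271.05, about 271 | 8.1% | 7% | 12.3 |

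The Catalan weight is 11.8 times the Aragonese one (271/23).

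**Shares.** The frame has 23 + 41 + 271 = 335 teams. Attended patients per team are 10,000, 7,500 and 12,000 (Study population).

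| | Frame teams | Sampled teams | Frame patients | Sampled patients |
|---|---|---|---|---|
| Aragón | 6.9% | 33.3% | 230,000 (6.1%) | 220,000 (33.9%) |
| Navarra | 12.2% | 33.3% | 307,500 (8.1%) | 165,000 (25.4%) |
| Catalonia | 80.9% | 33.3% | 3,252,000 (85.8%) | 264,000 (40.7%) |

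The document's own subject totals give the same picture: 350,000 / 850,000 = 41% Catalan.

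**Size of the error.** The regional rates are assumed. If Aragón and Navarra share one rate and Catalonia differs by d points, the error is d × (Catalan frame share − Catalan sample share).

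- Patient level: 0.858 − 0.407 = 0.451, giving 2.3, 4.5 and 9.0 points for d = 5, 10 and 20.
- Team level: 0.809 − 0.333 = 0.476, giving 2.4, 4.8 and 9.5 points.
- d = 0: no error at either level.

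**Spread between teams.** For d = 10, the between-region part of the pooled variance is (1/3)(2/3)(0.10²) = 0.0022 under equal allocation and 0.809 × 0.191 × 0.10² = 0.0015 in the frame. For comparison, team variance at the design ICC of 0.05 and a 70% rate is 0.05 × 0.7 × 0.3 = 0.0105, so this effect is small.

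**Cost of weighting.** Kish design effect = 66 × Σw² / (Σw)² = 2.02, so 66 teams act like about 33. With ICC 0.05 and a 50% rate, the standard error of the unweighted mean of 66 teams is √(0.05 × 0.25 / 66) = 1.4 points. Weighted, it is 1.4 × √2.02, about 2.0 points. Squared bias outweighs the added variance once 0.476d exceeds √(2.02 − 1) × 1.38 = 1.39 points, that is, d above about 2.9 points. This ignores the finite-population correction.

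**The case against.** The strongest reply is that a condensed article neither prescribes nor rules out weights, and that survey weighting is a detail an analysis plan would normally carry. This stands in part: a reader might infer that the sponsor has decided against weighting, and the document does not say so. It does, however, fix standard methods with each team as one observation for a pooled analysis. Followed as written, that gives equal weight to teams whose selection probabilities differ about 12-fold.

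Second, no pooled prevalence is set as a target. The objectives concern variability, related factors and intraclass correlation, and the study is sized by region. That is fair, and equal allocation is a sound choice for those purposes. But the outcomes include describing implementation and control, the analyses are to be run globally, and the Discussion generalises from the whole database. The pooled figures need a stated meaning.

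Third, part of the problem is already handled. Region-specific results are reported and are unaffected. Adjusting for record system would absorb the contrast between Catalonia and the other two regions in the multilevel models. A reader might infer that every global result is compromised; the documents do not support that for covariate associations.

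Fourth, the size can be overstated. Assumed rates of 60%, 70% and 80% in Aragón, Navarra and Catalonia give a pooled patient-level rate of 70.7% unweighted and 78.0% frame-weighted. It is tempting to call that gap larger than the planned regional precision. Those rates are invented, Aragón and Navarra share a record system, and no ±5-point precision is stated anywhere.

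**Conclusion.** The point holds for pooled descriptive results and should be settled before the global analysis. The selection fractions follow directly from the document's counts. The error relative to the three-region computerised frame is about 2.3, 4.5 or 9.0 points at patient level if only Catalonia differs by 5, 10 or 20 points, and zero if regions agree. The document gives no regional rates, so the direction and size of any actual error are unknown.

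The fractions are of computerised teams. Eligibility also requires wide use of the electronic record and agreement by more than 80% of staff, and the document does not count the teams that meet those criteria.

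The claim about Spanish NHS primary care is a separate coverage matter. A reader might infer that weighting would justify it. It would not: 81% of Aragón's teams lie outside the frame, as do Catalan teams outside the Catalan Health Institute (which manages almost 80% of that region's teams) and all other regions. Neither weights nor 850,000 records can restore teams that had no chance of selection.

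**What to change.** 1. State the population that the global descriptive estimates are meant to describe.
2. Weight those estimates by the inverse of the team selection probability within region, with region as stratum, using the actual counts of eligible and participating teams. The values 23/22, 41/22 and 271/22 are only a starting point. Alternatively, leave the pooled figures unweighted and label them as describing the sampled teams only.
3. Include region in the pooled multilevel models.
4. Keep the regional estimates as planned.
5. Limit the Discussion's conclusion to teams computerised before 2005 in the three regions, with Catalan Health Institute teams standing for Catalonia.

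No new patient data are needed, only team counts that the sponsor should hold from drawing the sample. The price of weighting is the design effect of about 2.0. The weighted global estimate will also lie close to the Catalan one, since Catalonia then carries about 86% of the patient weight. If that makes it of little use, labelling the unweighted figures is the cheaper choice. Narrowing the Discussion's claim costs nothing.

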### Study population: PHCT and patients

We performed random cluster sampling stratified by region with computerized PHCT used as unit of randomisation.

The inclusion criteria of the PHCT are: 1) computerization of the clinical records before the 1st of January 2005 to ensure familiarity with the system's use; 2) wide use of ECR, and 3) agreement to participate in the study by most of the health-care professionals working in each PHCT (> 80%).

For each computerized PHCT we select the ECRs of all subjects older than16 years as the unit of data collection. For the assessment of variability, the ECR of subjects receiving attention at least once in each of the study years will be extracted from the database. It is estimated that the average number of subjects receiving attention per year is around 70%. Thus in a PHCT in Aragon this figure would be around 10,000 patients, in Navarra around 7,500 and in Catalonia around 12,000. For the analysis of the evolution of health problems and related factors, subjects visited at least on one occasion during the 2006–2007 period and on a further occasion in 2008 will be included.

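### The unadjusted professional-level analysis treats professional means as independent although professionals are nested in teams, so its standard errors are too small for regional summaries and for factors that cluster by team

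*Protocol article*

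**What the plan says.** The Statistical analyses section of the protocol article sets out two steps for objectives 1 and 2, each done overall and by region.

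- **Cluster-level step.** Two kinds of cluster are named, the computerized PHCT and the health-care professional, and one method is given for both: the analysis "will be performed using standard parametric or non-parametric analytical methods, with cluster means or proportions as observations". No allowance for team is stated when the professional is the cluster.
- **Adjusted step.** "For the adjusted analysis we will perform regression analysis of individual level data using methods for clustered data, multilevel, hierarchical or random effects models". For these models the section states that "the attended individuals are nested within the health-care professional and the health-care professional within PHCT", and that "The PHCT and the health-care professional will be considered random effects".

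Under Study population, the teams were drawn at random within region, "with computerized PHCT used as unit of randomisation". The significance level is 1%, two-tailed (end of Statistical analyses). Other measures lists candidate factors by level. Training status, PAPPS adherence, record system and starting year, and assigned population are team factors. Workload, years in the PHCT and years of experience with electronic records are among the professional factors.

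**The concern.** Standard parametric and rank tests need independent observations. Team means meet this, since teams were sampled. Professional means do not: two professionals in one team share the team's organisation, record system and population, and the plan itself gives the team a random effect in its models. When the professional is the unit, the cluster-level step drops that effect.

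What is at stake is the precision reported for professional-level results. Intervals for a regional mean of professional proportions, comparisons between regions, and tests of professional characteristics that tend to be alike within a team would look more certain than they are. Identifying factors related to variability is a main aim of the study, so a spurious factor at this step could be reported as a finding. The adjusted models do not change the unadjusted results, which carry their own standard errors.

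**Working it through.** **Inputs from the article.** Team-level intraclass correlation 0.05 (Sample size and randomisation); 22 teams selected per region in 3 regions, so 66; significance level 1% two-sided. The article gives no figure for this analysis, so there is none to reproduce. The target of 20 teams per region does not bear on the point.

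**Inputs assumed.** Professionals per team, *k*, and the share of the variance of professional means that lies between teams, *ρ*. The article gives neither.

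**1. Purely between-team contrast** (region, a team factor tested on professional means, or the precision of a regional mean).

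Design effect DE = 1 + (k − 1)ρ. The standard error is understated by √DE. True level at nominal 1% = 2[1 − Φ(2.576/√DE)]. True coverage of a nominal 95% interval = 2Φ(1.96/√DE) − 1.

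| k | ρ | DE | √DE | True level | Coverage of 95% interval |
|---|---|---|---|---|---|
| 6 | 0.2 | 1 + 5×0.2 = 2.0 | 1.41 | 6.9% | 83% |
| 10 | 0.33 | 1 + 9×0.33 = 3.97 | 1.99 | 19.6% | 67% |
| 15 | 0.5 | 1 + 14×0.5 = 8.0 | 2.83 | 36.2% | 51% |

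Simulation of an ordinary t-test with a balanced team-level factor agrees: 6.5%, 19.4% and 37.1% with 66 teams; 6.6%, 19.6% and 36.0% with 22. The rank test fares no better: with 20 teams, k = 10 and ρ = 0.5, simulated levels were 28% (t-test) and 27% (Mann-Whitney).

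**2. Is that range of ρ plausible?** Take the article's 0.05 as the team share of patient-level variance. Assume a further professional share *v* of 0.02 to 0.10 and about 1,000 patients per professional. Then ρ = 0.05 / [0.05 + v + (0.95 − v)/1000].

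- v = 0.02: ρ = 0.05/0.0709 = 0.71
- v = 0.05: ρ = 0.05/0.1009 = 0.50
- v = 0.10: ρ = 0.05/0.1509 = 0.33

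Patient-level noise nearly vanishes from means over long lists, so a small patient-level correlation can become a large share of the variance of those means. With k from 5 to 20 these values give DE of 2.3 to 14.4 and true levels of 9% to 50%. If ρ is only 0.05 to 0.10, the true level over the same k is still 2% to 13%.

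**3. Factor that partly clusters by team.** If a share *c* of the factor's variance lies between teams, DE is about 1 + (k − 1)ρc. With c = 0.3 (assumed) the three scenarios give DE of 1.30, 1.89 and 3.10, and true levels of about 2.4%, 6.1% and 14%.

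**4. Factor distributed independently of team.** Here c is about 0 and DE about 1; simulated levels are 1.0% to 1.3%.

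**5. Factor exactly balanced within teams.** The team effect cancels from the contrast, so the true variance is about (1 − ρ) times the naive one and the test is conservative. True level = 2[1 − Φ(2.576/√(1 − ρ))] = 0.40%, 0.17% and 0.03% at ρ = 0.2, 0.33 and 0.5.

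**6. Team means as the unit.** Simulated level 0.8% to 1.1% with 20 or 60 teams, so that part of the plan holds its nominal level.

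**The case against.** The strongest reply is that the largest error rates need a test the plan does not clearly intend. Other measures sorts factors by level of analysis. Read with that list, the cluster-level sentence most naturally means team factors on team means, which is valid, and professional factors on professional means. A reader might infer that the plan's tests of training status, PAPPS adherence or assigned population are invalid. The documents do not support that, because the team-mean analysis is available for exactly those factors. This part of the objection stands.

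A reader might also infer that every professional-level test is too liberal. That is wrong too: the direction depends on how the factor is spread across teams, and for a balanced factor it reverses.

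Third, the nesting is handled where adjusted factor effects are estimated, the variance components come from random-effects methods, and a purely descriptive spread of professional proportions needs no independence. This stands, and it confines the problem to the unadjusted professional-level step.

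Finally, the article is condensed and detail may sit in a fuller plan. This carries less weight. The sentence is not silent on method: it fixes one method for both levels. Nor does matching factors to their own level remove the problem. Regional means and regional comparisons of professional proportions still take the full design effect, and factors such as experience with electronic records or workload may well run alike within a team.

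**Conclusion.** The point holds for the unadjusted professional-level analysis and no further. As written, it ignores the team. Provided team variance is above zero, standard errors are too small for regional or global means of professional proportions, for comparisons between regions, and for factors that cluster by team, including any team factor if it were tested on professional means. They are too large for factors balanced within teams and about right for factors unrelated to team.

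For a purely between-team contrast the understatement is 1.4 to 2.8 times, with a true level of about 7% to 37% at nominal 1%. This assumes 6 to 15 professionals per team and a between-team share of 0.2 to 0.5. These are illustrations, not the plan's actual error rates, since the article gives neither input. PHCT-level analyses, the adjusted multilevel models and the intraclass correlations are not affected. It should be corrected, because the remedy is cheap and uses a term the plan already has.

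**What to change.** In Statistical analyses, restrict standard tests on cluster means or proportions to the PHCT level, and state that PHCT factors are tested on PHCT means. For the professional level, analyse professional means in a linear mixed model with a random PHCT intercept, or use standard errors clustered on PHCT with small-sample degrees of freedom (22 teams per region is few for the uncorrected version). Apply the same to intervals for regional and global means of professional proportions.

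The cost is one sentence and one random term, with no new data. Some unadjusted p-values and intervals will become less favourable; those for factors balanced within teams may become sharper.
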